#### Trial duration

The study duration is set for 24 months from the date of Institutional Review Board (IRB) approval. However, this period may be extended based on the pace of participants enrollment.

#### Test Methods

##### Test design

This study is a randomized, multicenter, parallel design, clinical trial. After receiving sufficient explanation from the researchers involved in this study and voluntarily signing the consent form, participants who are deemed suitable for the study by reviewing the inclusion and exclusion criteria according to the protocol will be assigned a patient identification code. Blood tests will be performed, and they will be randomized to the acupuncture treatment group, electroacupuncture treatment group, and no-treatment control group at a later screening visit.

Each participant will have a screening visit, followed by randomization. If assigned to the acupuncture arm or the electroacupuncture arm, participants will attend bi-weekly visit for a total of 5 weeks, resulting in 10 visits for acupuncture or electroacupuncture, respectively. Subsequently, a follow-up assessment will be conducted 4 weeks later. The control group is required to attend three visits, designated as Visit 1, Visit 10, and Visit 11, respectively.

[figure not shown]

##### Randomization Methods and Blinding

- - 1. Overview

After the particioants have signed the informed consent form, they will be randomized to the acupuncture treatment group, the electroacupuncture treatment group, or the no-treatment control group at Visit 1, if they are deemed eligible for the study after reviewing the inclusion and exclusion criteria. Participants will be instructed on the procedures and visit dates, and will receive 10 treatments twice a week for 5 weeks (±3 days) according to the study schedule. All three arms will be assessed for efficacy 5 weeks (±3 days) after randomization and followed up at 9 weeks (±3 days).

- - 1. Randomization and stratification methods

Patients who agree to participate in this study will be assigned a screening number in the order of their written consent, and if more than one person is screened on a single day, the screening numbers will be assigned in the order of their consent. Randomization codes will be provided by an independent statistician or a third independent investigator with a 1:1:1 ratio of acupuncture, electroacupuncture, and no-treatment control groups. Randomization numbers will be generated using the blockrand package in R 3.4.2 or later, stratified by site at randomization, and block randomization will be used to ensure that the number of participants in each arm is approximately equal. At each site, participants will be assigned numbers based on the order of screening completion.

- - 1. Assignments

This study will use the sealed envelope method. The independent statistician or third independent investigator who generated the randomization code will place a piece of paper with the randomization code inside the opaque envelope, seal it, and give it to the authorized representative at each site. If a participant who has given written consent passes the screening assessment, the authorized representative will open the envelope in the order in which the screening assessment is completed, verify and record the participant's randomization code and assignment arm.

- - 1. Blindfold

This study is an open-label trial in which all arm assignments are not blinded to outcomes. However, we will blind the assessors who evaluate participants' symptoms separately from the treating physician to minimize possible bias in the assessment.

##### Trial Schedule

- - 1. Recruiting trial participants

Volunteers will be recruited through walk-in patients at each site or through open recruitment via outdoor advertising.

- - 1. Consent and assigning participant identification codes

After fully explaining the study, written informed consent will be obtained and a participant identification code will be assigned in this order.

If an employee of the clinical research organization or a student at his/her university wishes to participate, the study will be conducted only on participants unrelated to the study; the study will be fully explained to the employee or student who is motivated to participate voluntarily; and the employee or student will be guided to complete and sign an informed consent form only if he/she agrees. (Example: "I am an employee of a hospital or a student at a university, and I have been fully informed about the study and am motivated to participate voluntarily and sign the consent form.")

- - 1. Participants selection
       1. Demographic and sociodemographic information / other pre-treatment characteristics

Assign a screening number and collect demographic and sociodemographic information. The following will be recorded

- Whether and date of written consent
- Participant initials
- Age
- Blood pressure, height, weight
- Occupation
- Digestibility
- Exercise status and related information
- Smoking status and related information
- Drinking status and related information
- Sleep status and related information
- Obstetrics and gynecology information
- Pathways and motivations to participate in research
  - - 1. Medication history for coldhypersensitivity in the hands and feet / Other Organs

History and Medication History for Hand and Foot Cold: Conducted on Visit 0

Items related to Hand and Foot Cold (if applicable)

- Whether or not you've been diagnosed with coldhypersensitivity in the hands and feet
- Duration of cold feet morbidity (months)
- Previous treatment for cold feet

(medication / korean medical treatment (acupuncture / moxibustion / her bal medicine, etc.) / exercise therapy / psychotherapy / other complementary medications)

- Medications and treatments you are taking for coldhypersensitivity in the hands and feet
- Other medical and medication history items
- General physical exam items: Performed at every visit

Sensory, musculoskeletal, endocrine, multiple, urinary, reproductive, digestive, cardiovascular, nervous, dermatologic, and estrogenic systems. Obtain a history of renal, hematologic, lymphologic, respiratory, and other medical and medication history. Any significant findings o n examination at the initial visit should be recorded in the other organ systems section of the case record sheet, and any significant medical findings that meet the definition of an adverse event after initiation of the study procedure should be recorded on the adverse event sheet.

- - - 1. Visual Analog Scale (VAS)

Assess at each visit. At each visit, a VAS for the degree of coldhypersensitivity in the hands and feet will be completed by the participants with the assistance of the investigator.

- - - 1. Pattern Identification Questionnaire and Constitutional Diagnostic Questionnaire (KS- 15)

Administered at Visit 0.

Two principal investigators or a Korean medicine doctor will evaluate the participants.

The evaluator checks the items and marks ◯ on the most appropriate item to indicate the degree of the condition the participant has through the pattern.

The evaluator marks the corresponding pattern identification with a ◯.

- - - 1. Vital signs and height and weight measurements

Vital signs are assessed at every visit. Vital signs include blood pressure, pulse rate, and temperature. Height is measured only at Visit 0, and weight is measured at Visits 0, 10, and 11.

- - - 1. Determining conformance to inclusion/exclusion criteria

At Visit 0, consent, demographic and sociodemographic information, medical and medication history, laboratory tests, pregnancy test and chest x - ray, electrocardiogram, and thermometer measurements to determine if the participant meets the cold diagnostic criteria will be taken.

- - - 1. Check for changes in medical and treatment history

Inquire at each visit whether there have been any changes in medical and treatment history since Visit 0 (Screening). Inquire about any changes compared to what was identified in the drug history screening at Visit 0. If there are any changes in concomitant medications, document them in detail in the case record.

- - - 1. Clinical examination items

Obtain written informed consent and perform a 12-lead EKG, chest x-ray, and examination of the following on Visit 0

①Hematological tests: WBC, RBC, Hemoglobin, Platelet

②Blood biochemical tests: BUN, Creatinine, AST, ALT, r-GTP, Glucose

③Thyroid function test: free T4, TSH

④Urine and urine specimen tests: Blood, Urobilinogen, Bilirubin, Ketone, Protein, Nitrate, Glucose, pH, S.G, LEU, WBC, RBC

⑤Pregnancy test (women of childbearing age): Urine HCG

However, for Visit 10, the following checks are performed

①Hematologic tests; WBC, RBC, Hemoglobin, platelet

②Blood biochemical tests: BUN, Creatinine, AST, ALT, r-GTP

Systolic blood pressure greater than or equal to 180 mm Hg or diastolic blood pressure greater than or equal to 100 mm Hg as measured and averaged from the inclusion/exclusion criteria during Screening at Visit 0, Hemoglobin less than or equal to 7 g/dL for adult women (non-pregnant), WBC greater than or equal to 11,000/mm3, random plasma glucose less than or equal to 50 mg/dL or greater than 250 mg/dL, AST-ALT greater than or equal to 100 IU/L each, Creatinine greater than or equal to 2.0mg/dL, positive urinary hCG, presence of pulmonary TB lesions or pneumothorax other than inactive TB on chest x-ray, or cardiac disease such as arrhythmia or ischemic heart disease requiring treatment on electrocardiogram.

If there are no abnormal findings on the above examination and the patient's symptoms are considered, the patient will be included in the study.

The above tests will be performed by the laboratory of each medical institution participating in the clinical trial, and the korean medical hospital will refer the above tests to the laboratory of the western medical institution for testing.

- - 1. Randomization

Randomize patients to acupuncture treatment, electroacupuncture treatment, and no treatment control.

- - 1. Baseline checks

Baseline measurements of Visual Analogue Scale (VAS), body temperature (thermometer measurement), quality of life questionnaire (WHOQOL-BREF), quality of life assessment EQ-5D, coldness diagnostic questionnaire, weight, and vital signs will be taken from randomized participants. To minimize evaluators’s bias, one of the participating researchers will be assigned to complete the participants surveys and will not be involved in the acupuncture treatment or electroacupuncture treatment groups. The evaluator should not question the participant about the treatment.

- - 1. Needling and electroacupuncture methods:

Treatments for the acupuncture and electroacupuncture groups will be performed by researchers or study personnel who are not involved in the survey and evaluation.

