**Clinical trial flowchart**

| Recruitment and Informed Consent (Visit 0) |
| --- |

↓

| Screening |
| --- |
| Vital signs, height, weight, pathways to and motivation for study participation, demographic and sociodemographic surveys, obstetrical Informational history, medical history and medication history, general physical examination, thermometer measurement, VAS of coldhypersensitivity in the hands and feet, pattern identification questionnaire, laboratory test, Chest X-ray, ECG, Determination of exclusion criteria |

↓

| Randomization |
| --- |
| Acupucnture treatment group, Electroacupuncture treatment group, Control group |

↓

| Baseline (0week) Evaluation (Visit 1) |
| --- |
| Vital signs, weight, medical history and medication history and changes, constitutional diagnostics questionnaire (KS-15), general physical examination, thermometer measurement, VAS of coldhypersensitivity in the hands and feet, quality of life assessment questionnaire (WHOQOL-BREF), quality of life assessment EQ-5D, coldness diagnostic questionnaire, treatment, scheduling next visit |

↓

| Acupuncture or Electroacupuncture treatment (Visit 2~9) |
| --- |
| Acupuncture or electroacupuncture treatment for 5 weeks, vital signs, medical history and medication history and changes, general physical examination, thermometer measurement, VAS of coldhypersensitivity in the hands and feet, checking for adverse events, laboratory tests, scheduling next visit |

| Week 5 Evaluation (Visit 10) |
| --- |
| Vital signs, weight, medical history and medication history and changes, general physical examination, thermometer measurement, VAS of coldhypersensitivity in the hands and feet, quality of life assessment questionnaire (WHOQOL-BREF), quality of life assessment EQ-5D, coldness diagnostic questionnaire, checking for adverse events, laboratory tests, scheduling next visit |

↓

| Daily routine for 4 weeks |
| --- |

↓

| Week 9 Evaluation (Visit 11) |
| --- |
| Vital signs, weight, medical history and medication history and changes, general physical examination, thermometer measurement, VAS of coldhypersensitivity in the hands and feet, quality of life assessment questionnaire (WHOQOL-BREF), quality of life assessment EQ-5D, coldness diagnostic questionnaire, checking for adverse events |

↓

| Data cleaning and statistical processing |
| --- |

↓

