##### B. Visit 1 (D1)

1. Vital signs and weight measurement
2. Verify medical conditions/medications/treatments (check for changes in medical history and medications)

From Screening to Visit 1, investigate whether any new conditions, additional medications, or additional treatments have occurred. If yes, record in the Conditions/Medications/Treatments CRF form.

1. General physical exam

Determine if the patient has any of the conditions listed on the general physical examination form in the CRF at the time of the visit.

If present, circle yes and record in the abnormal findings section below.

V for none.

1. Thermometer measurements

At each visit, before and after treatment, bilateral temperatures at the anterior thigh (ST32) and dorsum of the foot (LR3), and at palm (PC8) and arm (LU4) will be measured using a non-contact infrared thermometer at a distance of, 3cm for three consecutive measurements and the median value excluding the highest and lowest values will be recorded.

1. Hands and feet coldness Visual Analogue Scale (VAS)

The VAS of coldhypersensitivity in the hands and feet will be completed by the participants with the assistance of the researcher. On the VAS, participants will mark an I for their level of hands and feet coldness.

O, V, not verbalized (to be precise)

1. Coldness diagnostic Questionnaire

Let the paticipants fill in the fields that need to be filled in.

The measurement must be performed by a practitioner.

1. The Korean version of the World Health Organization Quality of Life Scale (Short Form) (WHOQOL-BREF) and the EQ-5D Quality of Life Assessment

Check ◯ only for the most appropriate number.

Paper medical records keep the questionnaire and, if the medical record is electronic, the score, description, or item number. or itemized numbers. If this is difficult, create and store a clinical trial-specific paper medical record file.

1. Randomization

Randomize to no treatment, acupuncture treatment, and electroacupuncture treatment.

Record the predetermined randomization table number in the medical record and CRF.

1. Acupuncture or electroacupuncture

An investigator who does not participate in the survey will administer the treatment to the randomized acupuncture group or electroacupuncture group, respectively.

1. Specify your next visit date

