##### How to analyze validity variables

- - 1. Primary efficacy endpoint: Visual Analogue Scale (VAS) coldhypersensitivity in the hands and feet

The primary efficacy evaluation variables will be analyzed using the ITT group as the main analysis group, and the results of the PP group will be presented in addition. Repeated ANOVA, paired t-test, etc. will be performed to test whether there is a difference in the change in VAS score between the no-treatment control group and the acupuncture treatment group or the electroacupuncture treatment group. The comparison of the degree of improvement of VAS scores within each group will be performed by paired t-test using the difference between pre- and post- treatment VAS scores (VAS score at Weeks 5±3 days - VAS score at Visit 1).

- - 1. Secondary Validation Variables
       1. Body Temperature (BT; thermometer measurement): Repeated ANOVA is performed to test whether there is a difference in BT change between the acupuncture treatment group and the electroacupuncture treatment group. To compare the degree of improvement in BT within each group, a paired t-test will be performed using the difference between BT before and after acupuncture treatment (BT at Weeks 5±3 days - BT at Visit 1).
       2. WHOQOL-BREF Quality of Life Assessment Questionnaire: ANOVA and post hoc tests will be used to test the difference between each group. Comparison within each group is done by paired t-test using the difference in values before and after acupuncture treatment (value at Weeks 5±3 days - value at Visit 1).
       3. Pattern Identification Questionnaire:
          - This figure shows the distribution of the dialectical observables (dialectical indicators) in participants with coldhypersensitivity in the hands and feet. To determine the relationship between the dialectical indicators and the change in symptom VAS, an ANOVA test (non-parametric test if not normally distributed) and post hoc tests are performed for each indicator with the change in symptom VAS as the dependent variable.
          - Validity and reliability of the basic instrument are evaluated. The validity evaluation is

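### The protocol contradicts itself on whether the baseline VAS is taken before or after randomisation, so the primary change score may rest on a baseline rated after open-label allocation

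*Protocol*

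**What the plan says.** Four places in the protocol bear on the order.

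- **Trial Schedule.** A randomisation step comes first, then a step for baseline checks. That step covers "Baseline measurements of Visual Analogue Scale (VAS), body temperature (thermometer measurement", WHOQOL-BREF and EQ-5D, and ends with "coldness diagnostic questionnaire, weight, and vital signs will be taken from randomized participants".
- **Clinical trial flowchart.** The randomisation box leads by an arrow to "Baseline (0week) Evaluation (Visit 1", and that box contains the VAS.
- **B. Visit 1 (D1).** The VAS item ("On the VAS, participants will mark an I for their level of hands and feet coldness"), the coldness questionnaire and the quality-of-life scales are listed first. Then comes "Randomize to no treatment, acupuncture treatment, and electroacupuncture treatment", and treatment follows.
- **Test design.** Randomisation is said to happen at a subsequent screening visit, which would put it before Visit 1 altogether.

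The overview under Randomization Methods and Blinding and the two schedule tables put randomisation at Visit 1 but do not order it against the VAS.

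Three further facts matter:

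- On blinding: "This study is an open-label trial in which all arm assignments are not blinded to outcomes". Only the assessors are to be blinded.
- On who rates: "At each visit, a VAS for the degree of coldhypersensitivity in the hands and feet will be completed by the participants".
- On the change score, under How to analyze validity variables: "VAS score at Weeks 5±3 days - VAS score at Visit 1".

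**The concern.** A baseline should be fixed before anyone can react to the allocation. Here the outcome is a self-rating, the arms are not masked, and one arm receives nothing, which no participant can mistake for needling. If the Trial Schedule or the flowchart is followed, a participant may mark her baseline coldness already knowing whether she will be treated. If that knowledge moves the Visit 1 mark differently across arms and the movement is gone by Week 5, the difference enters the between-arm comparison of change with its sign reversed.

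The contradiction also leaves three sites free to follow different sections. The protocol does not ask for the time of the VAS relative to the opening of the envelope, so the data need not show which order was used.

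**Working it through.** **1. Order of steps**

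| Protocol section | Position of baseline VAS |
|---|---|
| Trial Schedule (randomisation, then baseline checks) | after randomisation; those measured are described as already randomised |
| Clinical trial flowchart | after randomisation |
| B. Visit 1 (D1) | listed before randomisation |
| Test design | randomisation at a further screening visit, hence before the Visit 1 VAS |
| Randomization overview; schedule tables | randomisation at Visit 1, order against the VAS not given |

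The sections cannot all be followed.

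**2. The plan's own sample size**

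Inputs from the section on the number of participants: SDs 1.03 and 1.17, difference 1.04, alpha 0.05, beta 0.2. The General principles make the test two-sided.

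- Pooled SD = √[(1.03² + 1.17²)/2] = 1.102.
- n = 2 × (1.96 + 0.84)² × 1.102² / 1.04² = 17.61, so 18 per arm.
- 18 / (1 − 0.25) = 24 enrolled per arm.

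The stated 18 and 24 reproduce. The printed formula shows 1.17 in place of 1.102, which would give 19.84. That is a separate slip and nothing here depends on it.

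**3. What an assumed shift would do**

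Assumptions: a two-arm t-test on the change score; SD of change 1.102; no true effect; a between-arm shift b in mean Visit 1 VAS that is absent at Week 5. The documents give no value for b.

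- Standard error = 1.102 × √(2/n): 0.367 at n = 18 and 0.318 at n = 24.
- Noncentrality = b / standard error. For b = 0.3 at n = 18: 0.3 / 0.367 = 0.817.
- P(reject) is the two-sided noncentral t probability with 2n − 2 degrees of freedom.

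| Assumed b (points) | Share of 1.04 | P(reject), 18 per arm | P(reject), 24 per arm |
|---|---|---|---|
| 0 | 0% | 5% | 5% |
| 0.2 | 19% | 8.3% | 9.4% |
| 0.3 | 29% | 12.5% | 15.2% |
| 0.5 | 48% | 26.3% | 33.7% |

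The 24-per-arm column is the closer match to the main analysis, which is ITT with last observation carried forward.

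**The case against.** The strongest reply is that the protective order is already in the protocol. The Visit 1 procedure is the detailed instruction, while the flowchart is a summary that is loose elsewhere: it puts the KS-15 questionnaire at Visit 1 when the schedule tables put it at screening. This is fair, and it makes the problem one of contradiction, not of a deliberately chosen post-allocation baseline. It does not settle the matter. List order in the visit procedures is not reliably time order, since Visits 2–9 and Visit 10 list treatment before the VAS. If the Visit 1 list is read equally loosely, the Trial Schedule and the flowchart are left as the explicit sequences.

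Blinded assessors do not answer the point, because the participant is the rater.

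A reader might infer that participants will know their arm when they mark the baseline, and that any shift passes straight into the treatment effect. The documents support neither:

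- No section says when the participant is told her arm. The site representative opens the envelope and records the code; disclosure before the VAS is possible but not stated.
- A shift that persists to Week 5, when participants also rate in knowledge of their arm, would cancel in the change score.
- The VAS form asks for the average over the past week, which may limit an on-the-spot reaction.

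Nor is it right that adjustment can do nothing. Adjusting for the Visit 1 VAS carries through only the slope times the shift: at an assumed slope of 0.5 and the same residual SD, a 0.3 shift leaves 0.15 and about 6.8% rejection at 18 per arm. The screening VAS, taken in all three arms before randomisation, is a baseline that allocation cannot have affected.

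**Conclusion.** The contradiction is certain from the text: two sections take the baseline VAS after randomisation, one lists it before, and a fourth places randomisation at a further screening visit. The bias is possible, not shown. It requires that the participant learns her arm before marking the VAS, that this moves her mark differently by arm, and that the movement has gone by Week 5. The size and direction are unknown, so the rejection rates of 8.3% to 26.3% (18 per arm) and 9.4% to 33.7% (24 per arm) show sensitivity to assumed shifts of 0.2 to 0.5 points and do not estimate the trial's error rate.

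It should still be settled before enrolment. It touches the baseline of the primary endpoint, an allocation-aware Visit 1 rating cannot be retaken afterwards, and the correction is nearly free.

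**What to change.** Bring Test design, the Trial Schedule and the flowchart into line with the order listed under B. Visit 1 (D1). State in each that at Visit 1 all baseline measures (VAS, temperature, WHOQOL-BREF, EQ-5D, coldness questionnaire) are completed and recorded in the CRF before the envelope is opened and the arm is disclosed. State also that the Visit 1 steps are to be done in the listed order.

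Add a sensitivity analysis of the Week 5 VAS adjusted for the screening VAS.

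The cost is wording and a site instruction. The visits, measurements and staff are unchanged, and the sample size stays at 18 evaluable and 24 enrolled per arm. The sensitivity analysis uses data already collected.
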